### Prebiotic and placebo products

Participants will be randomized to receive either prebiotic (oligofructose-enriched inulin; Synergy1, Beneo, Mannheim, Germany; 16 g/day) or an isocaloric matched placebo (maltodextrin; Agenamalt 20.222, Agrana Starch, Konstanz, Germany; 6.6 g/day). In Canada, inulin and oligofructose are regulated as food ingredients and have been used extensively in clinical trials in adults and children across a wide variety of health conditions [16]. The prebiotic and placebo are both white powders that dissolve completely in water. The study products will be provided to participants in identical opaque containers. Participants will be instructed to mix the daily dose of study product in a glass of water and consume it at their convenience with advice to consume it later in the day to minimize any daytime gastrointestinal discomfort that could arise. Given that an increase in fermentative substrate in the gut can increase flatulence, participants will be instructed to consume half of the daily dose for the initial 2 weeks in order to minimize gastrointestinal discomfort. Following the first 2 weeks, participants will consume the full daily dose for the remainder of the 6-month intervention portion of the study. At the end of the 6 months, the participants will discontinue the study products and a 3-month wash-out period will occur. This study is designed to examine the effects of prebiotic independent of any other diet or exercise intervention; therefore, subjects will be encouraged to maintain their regular lifestyle, to eat until comfortably full and not to consciously try to gain or lose weight throughout the study. Routine individual management of knee osteoarthritis that is in place at the beginning of the trial will continue throughout the duration of the study.

### Data collection

The overall study design is depicted in Fig. 1. Participants will be assessed at the start of the diet intervention period (baseline = month 0), 3 months, 6 months (end of the diet intervention period), and 9 months (3-month wash out period following the end of the diet intervention). The primary outcome will be the change in performance-based tests in adults with obesity and knee osteoarthritis treated for 6 months with oligofructose-enriched inulin or placebo. Change in performance-based tests (30-s chair stand test, 40-m fast-paced walk test, time up & go, hand grip strength, and 6-min walk test) will be assessed by a subset of Osteoarthritis Research Society International (OARSI) tests for physical function in individuals with knee osteoarthritis. The secondary outcomes include change in knee pain, change in body composition (fat mass and lean mass), and change in quality of life in adults with obesity and knee osteoarthritis treated for 6 months with oligofructose-enriched inulin or placebo. To gain a deeper mechanistic understanding of the influence of the prebiotic on physical performance, gut microbiota composition, as well as serum inflammatory and metabolomics markers will also be assessed.

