#### Secondary objectives

The secondary objectives are to determine if a 6-month prebiotic intervention can reduce knee pain, alter body composition (fat mass and lean mass), and improve quality of life. A mechanistic understanding of the potential changes will be investigated by examining changes in gut microbiota, serum inflammatory, and metabolomic markers in participants treated with the prebiotic supplement or placebo.

We hypothesize that prebiotic oligofructose-enriched inulin will reduce systemic inflammation, thereby alleviating knee joint pain and improving knee joint function. The intervention would be successful if it reduced knee joint pain sufficiently to enable participants to engage in a future exercise intervention with the goal to further increase knee joint function and reduce body fat, and thereby delaying/preventing the need for aggressive surgical intervention such as knee joint replacement.

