Improvement from baseline will be defined by an increase in the number of repetitions (30 s chair stand test), an increase in strength (hand grip strength), a reduction in the time to perform the 40-m fast-paced walk test, time up & go, or an increase in the distance covered for the 6-min walking test.

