### Analysis

Statistical analysis will be performed using SPSS 26.0 software (IBM, New York, USA). Results will be considered statistically significant if *p* ≤ 0.05. Baseline descriptive data between the prebiotic and placebo groups will be compared using chi-square for categorical variables and t tests for continuous variables. The primary analysis will be on an intent-to-treat basis, with a secondary analysis performed on a per-protocol basis with all subjects that complete the intervention. The primary outcome measurement of performance-based tests will be expressed as mean with standard deviation and analyzed using a two-way mixed model ANOVA (2 × 4) with a within-subject factor (time) of 4 levels (0, 3, 6, and 9 month time points) and one between factor (group) of 2 levels (prebiotic and placebo). A similar statistical approach will be used to test differences in the secondary outcome measurements including DXA body scans, blood tests, stool collection, and questionnaires. For the microbiota analysis, Phyloseq R package will be used for downstream analysis. Alpha diversity will be measured by calculating the Shannon and Simpson index. Beta diversity will be evaluated using non-metric multidimensional scaling (NMDS) on Bray-Curtis dissimilarity matrix. Differential abundance analysis between groups will be carried out using LEfSe conda package. To account for multiple comparisons, a false discovery rate (FDR) correction will be applied and significance set at *p* ≤ 0.05.

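### Five performance tests share primary status with no ranking or success rule, and the only multiplicity sentence is not tied to them; if unadjusted, the chance of a false-positive primary result is about 13–23%

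*Protocol article*

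**What the plan says.** Under Data collection, the protocol article states: "The primary outcome will be the change in performance-based tests in adults with obesity and knee osteoarthritis treated for 6 months". The next sentence lists the components: "Change in performance-based tests (30-s chair stand test, 40-m fast-paced walk test, time up & go, hand grip strength, and 6-min walk test". The section on primary outcome measurements then describes all five on equal terms. Each has its own unit: repetitions, metres per second, seconds, grip force and metres.

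The Analysis section opens with a general threshold: "Results will be considered statistically significant if *p* ≤ 0.05". The primary outcome is to be "analyzed using a two-way mixed model ANOVA (2 × 4) with a within-subject factor (time) of 4 levels", with group as the other factor. Neither factor indexes the test.

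Multiplicity appears once, at the end of the same section: "To account for multiple comparisons, a false discovery rate (FDR) correction will be applied". That sentence follows the description of alpha diversity, beta diversity and differential abundance, and it sets its own threshold of p ≤ 0.05.

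Under Secondary objectives there is a statement about success that concerns pain: "The intervention would be successful if it reduced knee joint pain sufficiently to enable participants" to take up exercise later. It gives no amount of pain reduction and no statistical criterion.

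**The concern.** Which outcome is primary, and what result would count as success on it, are matters for the protocol. Here five separately measured tests carry the label, and the text does not say whether one, some or all must differ between groups. Five tests at 0.05 each give five chances of a positive primary finding, and a mixed set of results would have no agreed interpretation. The FDR sentence could reduce the problem, but the text does not say that it applies to these tests.

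At stake is the error rate attached to the trial's main claim and the reader's ability to tell a positive trial from a negative one. The pain sentence adds some looseness, because the only use of the idea of success in the objectives refers to a secondary outcome.

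**Working it through.** **Inputs from the protocol article**
- Number of tests with primary status: 5 (Data collection; primary outcome measurements).
- Threshold: p ≤ 0.05 (Analysis). Sidedness is not stated; two-sided is assumed.
- Sample size for the primary outcome: n = 21 for 90% power at alpha 0.05, based on isokinetic function, which is not one of the five tests (Sample size).
- Recruitment: 30 per group (Sample size), with 30% more than required to allow for withdrawals (Discussion).
- Correlation among the five tests: not given. It is an assumption here, shown from 0 to 0.9.

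**The plan's own figures.** The article states no family-wise error rate. The n = 21 cannot be reproduced because no effect size or standard deviation is given. The step to 30 does reproduce from the larger requirement, the n = 23 for fat mass: 23 × 1.30 = 29.9, rounded up to 30.

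**Error rate if the five tests are unadjusted, all nulls true**

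Independent tests: 1 − (1 − 0.05)^5 = 1 − 0.7738 = 0.226.

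Correlated tests: 500,000 simulated sets of five equicorrelated normal statistics, counting sets with at least one two-sided p ≤ 0.05. The favourable-only column counts sets with at least one z > 1.96. The last two columns apply an adjustment to the same sets.

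| Assumed correlation | Any of five, two-sided | Any favouring prebiotic | Benjamini–Hochberg over the five | Holm over the five |
|---|---|---|---|---|
| 0 | 22.6% | 11.9% | 5.0% | 4.9% |
| 0.3 | 20.7% | 10.4% | 4.8% | 4.6% |
| 0.5 | 18.2% | 9.1% | 4.5% | 4.2% |
| 0.7 | 14.8% | 7.4% | 3.9% | 3.4% |
| 0.8 | 12.7% | 6.3% | 3.6% | 3.0% |
| 0.9 | 10.1% | 5.1% | 3.3% | 2.3% |

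For comparison, a single two-sided test gives 5%, or 2.5% in the favourable direction. If four tests correlate at 0.7 with each other and grip strength at 0.3 with the rest, the unadjusted two-sided rate is 16.9%.

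**Check with the planned model.** The group-by-time F test of the 2 × 4 ANOVA was simulated with 30 per group (20,000 trials), counting any of five at p ≤ 0.05. The rate was 22.3% at correlation 0, 18.6% at 0.5 and 13.4% at 0.8. This agrees with the table.

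**Power cost of adjustment.** Assume that n = 21 is per group and refers to a two-sample t test. The effect that gives 90% power is then d = 1.03. The normal approximation is (1.960 + 1.282) × √(2/21) = 1.00. Holm requires the smallest of five p-values to be at most 0.05/5 = 0.01. At d = 1.03, a test at 0.01 has 73% power with 21 per group and 90% with 30 per group. The 90% therefore returns only if all 30 per group are evaluable, which leaves no allowance for withdrawals.

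**The case against.** The strongest defence is that the FDR sentence closes the whole Analysis section and is not expressly confined to the microbiota. If it means Benjamini–Hochberg over the five tests, the all-null error is about 4–5%. That reading cannot be excluded. It is the less natural one, because the sentence directly follows the microbiota methods and restates a threshold that the section has already set. Even on the generous reading the scope is unstated, and FDR control does not hold the family-wise error once some of the five effects are real.

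It is also fair to say that the mechanics of multiplicity adjustment can be left to an analysis plan that is not shown. That does not extend to which outcome is primary, which the article itself fixes, and fixes as five unranked tests.

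Four stronger readings may tempt a reader. The text does not support them.
- **An any-one-of-five success rule.** A reader might infer it from the sentence containing "a reduction in the time to perform the 40-m fast-paced walk test, time up & go, or an increase in the distance covered". That sentence gives the direction that counts as better on each test. It sets no trial-level rule.
- **Hand grip as irrelevant to the objective.** The article describes grip as a measure of physical function as well as of muscle strength, and the primary objective covers physical performance as well as knee function.
- **Further inflation from the interim analysis.** The article announces one when half the participants have completed the intervention, with continuation decided by the steering committee. It states no efficacy test at 0.05, so no additional error can be computed.
- **Licence to claim success on pain with a null primary result.** The sentence is an aspiration about a later exercise programme, has no criterion, and pain is consistently listed as secondary.

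**Conclusion.** The point holds. Five tests have equal primary status at p ≤ 0.05, without ranking, composite or success rule, and the one multiplicity sentence is not tied to them. If they are unadjusted, the chance of at least one two-sided false-positive primary result is about 13–23%, or about 6–12% counting only results in favour of the prebiotic. These figures assume that all nulls are true and that pairwise correlations lie between 0.8 and 0, which the article does not give; at 0.9 the two-sided figure is still 10%. If the FDR correction does cover the five tests, the figure falls to about 4–5%, and what remains is the missing ranking and success rule. The inflation is therefore conditional on how the FDR sentence is read. The lack of a defined primary result is not.

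**What to change.** Before any unblinding:
1. Choose one of two routes. Either apply Holm at 0.05 across the five tests, or have the investigators pre-specify one primary test (or a fixed testing order) and make the rest secondary.
2. State which families of comparisons the FDR correction covers, and whether the five performance tests are among them.
3. Reword the success sentence under Secondary objectives so that success on the primary objective is judged by the rule in step 1, with pain reported as a secondary result.

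This changes wording only and needs no new data. Under Holm, the smallest p must be at most 0.01. At the back-solved d of about 1.03 (n = 21 taken as per group), that cuts power from 90% to about 73% with 21 per group. Naming one primary test keeps the full 0.05 and avoids this loss, at the price of demoting the other four. A fixed order also starts at 0.05, but testing stops at the first non-significant result.

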**Fig. 1 Fig1:**
[figure not shown]
Schedule outlining the enrolment, interventions, and assessments for the proposed randomized controlled trial. Following eligibility assessment and informed consent collection (month 0), participants will be randomly allocated to either prebiotic (oligofructose-enriched inulin; 16 g/day) or placebo (maltodextrin; 6.6 g/day). Follow-up assessments will be performed at 3 and 6 months. After the 6 months’ intervention period, participants will stop taking study products and will be assessed again at 9 months to determine the persistence of the effects

### Primary outcome measurements

#### Performance-based tests

The 30-s chair stand test is a test of lower body strength, endurance, and dynamic balance. Participants will be instructed, from a sitting position on a chair (44 cm seat height without arms), to stand up completely with fully extended hips and knees then completely return to the sitting position. This is repeated for 30 s and the number of repetitions is recorded [36–38].The 40-m (4 × 10m) fast paced walk test is a test of short walking distance and changing direction while walking as fast as possible without running. Participants will be instructed to safely walk as fast as possible, along a 10-m walkway, and then turn around a cone, and return to the starting point and repeat again for a total of 40 m. The time of the test is recorded to the nearest 100th of a second and expressed as speed (m/s) by dividing the distance (40 m) by the time (s) it took to perform the test [38].The time up & go is a transition test of ambulatory activity, including strength, agility, and dynamic balance. From a sitting position on a chair (44 cm seat height without arms), participants will be asked to stand up, walk to a cone 3 m away, turn around the cone, and return to sit back in the chair as fast and as safe as possible. Time is recorded in seconds to the nearest 10th of a second [37–39].The 6-min walk test is a test of aerobic capacity and long distance walking activity. Participants will be instructed to walk as quickly as possible along a 40-m walkway, turn around a cone, return to the starting position, and repeat it again for 6 min to cover as much ground as possible. The distance walked over the 6 min is recorded in meters [37, 38, 40, 41].The hand grip strength test is an objective measure of overall body muscle strength and physical function [42] as well as an important measure for frailty [43]. Participants will be asked to comfortably sit in a chair with both knees and hips flexed at 90°. Next, participants will hold the hand grip device (Jamar®, Patterson Medical, Warrenville, IL, USA) at 90° elbow flexion and be instructed to exhibit the greatest force possible, followed by a second trial with a 3-min rest interval between trials.

Improvement from baseline will be defined by an increase in the number of repetitions (30 s chair stand test), an increase in strength (hand grip strength), a reduction in the time to perform the 40-m fast-paced walk test, time up & go, or an increase in the distance covered for the 6-min walking test.

### Secondary outcome measurements

#### Outcomes related to knee joint pain

Numerical pain rating scale (NPRS) for knee pain: Participants will be asked to rate their pain intensity by selecting a number from 0 (no pain) to 10 (worst possible pain).

Knee injury and osteoarthritis outcomes score (KOOS): Participants will be asked to complete the self-administered KOOS questionnaire every 3 months, which consists of 5 subscales: pain, symptoms, function in activities of daily living, function in sports and recreation, and knee-related quality of life [44]. The questionnaire score ranges from 0 to 100, showing severe knee problems to no knee problems, respectively.

##### Pain medication questionnaire

At 0, 3, 6, and 9 months, participants will be asked to record knee pain medication name, dosage, and frequency over the past 7 days prior to coming to the test site.

#### Anthropometric measures

##### Anthropometrics

Current age, height, and sex will be collected. Weight will be measured using a calibrated balance beam scale at the start of the protocol to assess BMI and will be monitored every 3 months throughout the intervention period. Body composition will be assessed by dual energy x-ray absorptiometry (DXA; Hologic QDR 4500, Hologic, Inc., Bedford, MA).

##### Physical activity

Participants will be instructed to maintain their current level of physical activity throughout the study. Physical activity will be monitored every 3 months using a modified Godin’s leisure time exercise questionnaire, based on weekly exercise average intensity (strenuous, moderate, and mild) over the past month [45]. Furthermore, objective physical activity will be assessed by an accelerometer at the hip level at 30 Hz (ActiGraph Link®, Philips Healthcare; Andover, MA) for five consecutive days every 3 months. The metabolic equivalent (METs) will be calculated based on counts per minute. Counts per minute will be classified using already determined tri-axial vector magnitude cut-points for light, moderate, hard, or very hard using ActiLife6 software (ActiGraph, Pensacola, FL) [46].

#### Outcomes related to quality of life

Quality of life will be measured every 3 months using the SF-36 Health Survey questionnaire. This is a 36-question self-administered questionnaire to measure health on multi-dimensions, covering functional status, wellbeing, and overall evaluation of health [46]. Gastrointestinal feelings and bowel habits will be assessed every 3 months using our standard gastrointestinal feeling form that rates abdominal discomfort, bloating, flatulence, rumblings of stomach, and number of bowel movements [30].

### Food records

Participants will be encouraged to maintain their habitual diet intake throughout the study. Food and beverage will be assessed using a 3-day (two weekdays and one weekend day) food record every 3 months. This information will be analyzed with FoodWorks 18.0 software with the Canadian Nutrient File (The Nutrition Company, Long Valley, NJ) [31].

### Gut microbiota and inflammation related outcomes

Participants will be instructed on proper methods for stool sample collection and all materials provided in a convenient stool collection kit. Participants will collect 2 tablespoons of stool every 3 months. The container will be sealed, placed in a biohazard bag, transported to the lab, and stored at − 80 °C until processed.

#### Fecal microbiota analysis

Microbiota composition will be assessed as previously described [24, 47]. Bacterial genomic DNA will be extracted from stool samples using a fastDNA spin kit for feces (MP Biomedicals, Santa Anna, CA) and sequenced by the University of Calgary Centre for Health Genomics and Informatics using the Illumina 16S sequencing platform to amplify the V3-V4 region. Sequencing data from the MiSeq will be demultiplexed and converted to fastq format using Illumina’s bcl2fastq software. CutAdapt will be used to remove primers from reads and perform initial quality trimming. Following primer removal, length sequences of shorter than 10 bases pairs will be removed, and quality trimming threshold set at Q20. R package DADA2 will be used to infer amplicon sequence variants. Chimeric sequences will be removed, and taxonomic assignment performed using the RDP classifier and RDP database as reference.

#### Fecal short-chain fatty acid concentration

Reverse-phase high-performance liquid chromatography will be used as previously described to measure short-chain fatty acids, key metabolites produced by the gut microbiota, that act as signaling molecules to host tissues [48].

#### Serum endotoxin and inflammatory markers

Blood collected every 3 months by an experienced technician will be allowed to clot, serum collected, and then aliquots stored at − 80 °C until used. Serum will be used to measure endotoxin (lipopolysaccharide) using a PyroGene recombinant factor C endotoxin detection kit (Lonza, Walkersville, MD) [49]. Serum inflammatory biomarkers will be assessed using the 42-plex protein array panel at Eve Technologies (Calgary, AB) [50]. The 42-plex assay is a comprehensive panel of cytokines and chemokines that will help in elucidating the systemic effects of prebiotic exposure on systemic and local (knee joint) inflammation.

#### Serum metabolomics

Metabolomic profiles in serum will be assessed using proton nuclear magnetic resonance (^1^H NMR) spectroscopy as previously described [51, 52]. Blood metabolites can be useful in elucidating pathways by which interventions such as diet alter physiological outcomes [51, 52].

##### Compliance

Participants will be asked to return the product containers to assess compliance and actual product intake. Participants will purchase their own food and maintain their habitual food intake during the intervention period which will be monitored via completion of a 3-day food record every 3 months. Any changes or amendments to the protocol will be conveyed to the research ethics board via an official modification request and participants will be informed via electronic mail and/or phone.

### Sample size

Since there are no previous clinical trial studies assessing prebiotic supplementation in adults with co-morbid obesity and knee OA, the sample size calculation is based on data from relevant studies in obesity treatment. We have calculated sample size for both the primary and a secondary outcome. For the primary outcome, we used changes in isokinetic function for patients suffering from knee OA treated with an exercise intervention [53], showing that an *n* = 21 would provide 90% power at an alpha level of 0.05. For the secondary outcome, we used changes in body composition from a randomized placebo-controlled trial we conducted previously [25]. The calculation determined that an *n* = 23 would provide 90% power at an alpha level of 0.05 based on the decrease in fat mass in prebiotic versus placebo in adults with overweight or obesity. Given the length of the study (9 months) and the expected dropouts observed in intervention studies with dietary modification, additional participants will be added to account for potential dropouts. Therefore, *n* = 30 participants per treatment group (*n* = 60 total) will be recruited.

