This double-blind, placebo-controlled clinical trial is not without limitations and steps have been taken to reduce potential confounders and bias. First, this is an extensive and long-term study (9 months in total) and we speculate that participants may withdraw from the study. In order to accommodate for such losses, we will enroll 30% more participants than required on our sample size calculations. In some patients, oligofructose and inulin can cause result in increased flatulence and bloating. To minimize abdominal discomfort, participants will be instructed to start on a lower dose for the first 2 weeks to allow the digestive system to adjust to the increased intake of fermentable substrate. Finally, given the long duration of the study, patients might undergo lifestyles changes from the time of baseline assessments. To be able to monitor potential changes, dietary intake will be recorded with 3-day food records and physical activity monitored with self-report questionnaire and accelerometer results at 3 month intervals.

The work proposed here has the potential to identify a novel therapy that could alleviate some of the pressure on the growing demand for aggressive OA treatments such as total knee joint replacement at younger ages. Less aggressive, yet effective, conservative treatment options have the potential to address the growing prevalence of co-morbid obesity and knee OA by delaying the need for joint replacement or ideally preventing its need altogether. The results of this clinical trial will provide the first evidence regarding the effects of prebiotic supplementation on knee joint function and pain in adults with obesity who are also suffering from knee OA. If successful, the results may provide a simple, safe, effective, inexpensive, and easy to adhere intervention to reduce knee joint pain and improve the quality of life of adults with co-morbid knee OA and obesity.

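### The 90% power stated for the primary outcome is borrowed from another endpoint and another treatment, so it is unsupported for the five performance tests; the enrolled 60 follows from the fat-mass calculation

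*Protocol article*

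**What the plan says.** The Sample size section of the protocol article notes that no earlier prebiotic trial exists in adults with both obesity and knee OA. It then says that "the sample size calculation is based on data from relevant studies in obesity treatment". Two calculations follow.

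- **Primary outcome:** "For the primary outcome, we used changes in isokinetic function for patients suffering from knee OA treated with an exercise intervention". This gives n = 21, which "would provide 90% power at an alpha level of 0.05. For the secondary outcome" the text turns to fat mass.
- **Secondary outcome:** n = 23 for 90% power at the same alpha, from the fall in fat mass on prebiotic versus placebo in the team's own previous randomised trial.

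The section ends with 30 per group, 60 in total, to allow for dropout. The Discussion describes the allowance: "we will enroll 30% more participants than required on our sample size calculations".

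The endpoint is defined under Data collection: "The primary outcome will be the change in performance-based tests in adults with obesity and knee osteoarthritis". The tests are listed there as "30-s chair stand test, 40-m fast-paced walk test, time up & go, hand grip strength, and 6-min walk test". On treatment, the section on the study products says: "This study is designed to examine the effects of prebiotic independent of any other diet or exercise intervention". Participants are also told to keep their physical activity unchanged.

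**The concern.** A power statement holds for one endpoint, one contrast and one assumed effect. Here the effect behind n = 21 comes from isokinetic muscle testing after exercise. None of the five primary tests is isokinetic, and no isokinetic measure appears among the secondary or mechanistic outcomes. The contrast in this trial is supplement against placebo with exercise held constant. Endpoint and treatment therefore both differ, and the article makes no argument for carrying the effect over.

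This is the only power figure given for the primary outcome. If the trial finds no difference, the 90% invites the reading that a worthwhile effect on function has been ruled out with high confidence. The plan as written does not support that reading.

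**Working it through.** **Inputs.** From the article: n = 21 (primary) and n = 23 (fat mass), 90% power, alpha 0.05, 1:1 allocation, 30 per group enrolled, 30% allowance. Assumptions: two-sided testing; 21 and 23 are per group, as the 30 per treatment group implies; one test compared between groups at one time point. The article gives no mean difference, SD or standardised effect, so n = 21 cannot be reproduced forwards. It can only be solved backwards for the effect it implies.

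**Step 1: effect implied by the stated n.** By the normal approximation, d = (z₀.₉₇₅ + z₀.₉₀) × √(2/n) = (1.960 + 1.282) × √(2/n). The last column uses the noncentral t.

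| n per group | Source of n | d, normal approx. | d, noncentral t |
|---|---|---|---|
| 21 | isokinetic function | 1.00 | 1.03 (1.025) |
| 23 | fat mass | 0.96 | 0.98 |
| 30 | enrolled, no dropout | 0.84 | 0.85 |

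Read as a between-group comparison, n = 21 thus presumes a difference of about one SD.

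**Step 2: which calculation sets the enrolment.** 23 × 1.3 = 29.9, rounded to 30. For the other figure, 21 × 1.3 = 27.3, which does not lead to 30. The larger requirement, fat mass, governs. Of 30 enrolled per group, 23 remain after 23% dropout (1 − 23/30) and 21 after 30% (1 − 21/30).

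**Step 3: power across assumed true differences on one primary test** (unadjusted two-sample t-test, two-sided 0.05).

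| True difference (assumed) | 21 per group | 23 per group | 30 per group |
|---|---|---|---|
| 0.3 SD | 16% | 17% | 21% |
| 0.5 SD | 35% | 38% | 48% |
| 0.8 SD | 72% | 76% | 86% |
| 1.0 SD | 89% | 91% | 97% |

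Power runs from low to above 90% depending on an effect that the article does not state.

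**Step 4: allowance for baseline.** With baseline as a covariate, the detectable d is multiplied by √(1 − ρ²): 0.866 at ρ = 0.5 and 0.714 at ρ = 0.7 (both assumed).

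- 30 per group: 0.851 × 0.866 = 0.74 SD; 0.851 × 0.714 = 0.61 SD.
- 23 per group: 0.977 × 0.866 = 0.85 SD; 0.977 × 0.714 = 0.70 SD.

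An analysis of simple change scores has the factor √(2(1 − ρ)) instead: 1.00 at ρ = 0.5 and 0.775 at ρ = 0.7. At 30 per group that gives 0.85 SD and 0.66 SD.

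**The case against.** The strongest reply is that nothing in the trial depends on the borrowed figure. Deleting n = 21 leaves the 60 unchanged, because n = 23 governs and comes from a placebo-controlled prebiotic trial. The proxy is also disclosed: the article says that no direct precedent exists and names the borrowed endpoint and treatment. It concerns the same disease, and the chair stand is itself described as a test of lower-body strength. All of this stands, and it is why the severity is moderate. It does not make the 90% a statement about the five tests, since fat mass is a secondary outcome and disclosing a proxy does not show that its effect transfers.

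A second reply is that unadjusted figures are pessimistic, because the planned 2 × 4 mixed ANOVA includes baseline. This stands in part. With baseline as a covariate (ρ 0.5 to 0.7), power at 30 per group is 59 to 76% for a true 0.5 SD and 94 to 99% for 0.8 SD. The size of the gain depends on how baseline is used, as Step 4 shows.

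Third, a full protocol exists and is not shown. The effect size and SD may be there, so their absence from the article is not held against it. The point rests only on the mismatch that the article itself states.

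Some further inferences are tempting and are not supported:

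- That n = 21 came from a within-group before-after change. The cited study is not at hand, and one clause does not settle it.
- That 21 might be a total. The 30 per treatment group implies per group.
- That the 30% allowance is wrong because 30/21 = 1.43. It is applied to the larger requirement and is coherent.
- That the detectable difference must be computed at a Bonferroni level for five tests. Multiplicity is a separate question.

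**Conclusion.** The point holds. The article attributes 90% power to the primary outcome on the strength of an endpoint it does not measure and a treatment it does not give. The claim is unsupported for the five performance tests.

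A reader might go further and conclude that power is below 90%, or that the trial can detect only very large differences. The documents do not show either. True power cannot be computed from the article: at a true 1.0 SD, 30 per group would give 97%, while at 0.5 SD it would give 48% unadjusted. What can be stated is the difference detectable with 90% power on one test at two-sided 0.05. This is 0.85 SD (30 per group) to 0.98 SD (23 per group) unadjusted, or about 0.61 to 0.74 SD and 0.70 to 0.85 SD with baseline as a covariate. These figures assume a single between-group comparison at one time point and, for the adjusted values, a baseline correlation of 0.5 to 0.7. They are not the power of the group-by-time test over four visits.

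Severity is moderate: the enrolled number, the analysis and the estimates are unaffected, but the stated assurance about the primary outcome is not earned.

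**What to change.** In the Sample size section:

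1. Withdraw the statement of 90% power for the primary outcome.
2. Say that 60 participants follow from the fat-mass calculation (23 per group plus 30%).
3. Name one primary test and report the smallest between-group difference detectable with 90% power at the alpha actually used, for 30 and for 23 evaluable per group. Give it in the test's own units, with the SD from published data or from the blinded pooled data of enrolled participants.
4. Quote a baseline-adjusted figure only if the primary analysis uses baseline in that way, and give the correlation assumed.

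The cost is a rewritten paragraph and a less favourable stated figure. Enrolment does not change.
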